# Design of a phase II randomised, double-blind, placebo-controlled, dose-finding trial of BI 1819479 in patients with idiopathic pulmonary fibrosis

**DOI:** 10.1183/23120541.00973-2025

**Published:** 2026-03-16

## Abstract

**Background:**

Current treatments for idiopathic pulmonary fibrosis (IPF) slow but do not stop/reverse disease progression. The lysophosphatidic acid (LPA) axis is identified as a therapeutic target for IPF.

**Objective:**

This study aims to assess BI 1819479, an LPA pathway inhibitor, in patients with IPF (ClinicalTrials.gov Identifier: NCT06335303).

**Methods:**

In this placebo-controlled, phase II trial, patients will be randomised (2:1:1:1) to receive one of three oral doses of BI 1819479 or placebo, stratified by nintedanib/pirfenidone use. Patients aged ≥40 years with IPF, forced vital capacity (FVC) ≥45% of predicted normal and haemoglobin-corrected diffusing capacity for carbon monoxide ≥25% of predicted normal at screening will be included. Patients with relevant airway obstruction (pre-bronchodilator forced expiratory volume in 1 s/FVC <0.7), acute IPF exacerbation ≤12 weeks prior to screening, treatment with immunosuppressive medications (other than oral corticosteroids) or prednisone >15 mg·day^−1^ or equivalent, will be excluded. Treatment with approved IPF treatments (nintedanib/pirfenidone) is allowed if at a stable dose for ≥12 weeks prior to trial entry. Patients will be treated until completing 52 weeks, or 24 weeks after the last patient is randomised, whichever occurs first. The primary end-point is the annual rate of FVC decline (mL·year^−1^) assessed up to 52 weeks; the secondary end-point is absolute change from baseline in FVC at week 24. Safety will be assessed throughout.

**Conclusion:**

This trial evaluates the efficacy, safety and dose range of BI 1819479 in patients with IPF, offering a potential additional treatment option, and will establish appropriate dosing for phase III trials.

## Background

Idiopathic pulmonary fibrosis (IPF) is a progressive fibrosing interstitial lung disease (ILD) with a variable and unpredictable course [1, 2]. The disease trajectory is characterised by increasing respiratory symptoms, worsening pulmonary function, unpredictable episodes of acute respiratory decline, and ultimately death [2].

Nintedanib and pirfenidone are currently the only approved treatments for IPF and are the recommended standard of care per American Thoracic Society (ATS)/European Respiratory Society (ERS)/Japanese Respiratory Society (JRS)/Latin American Thoracic Association (ALAT) 2022 clinical practice guidelines [3–5]. However, while these treatments can slow disease progression, they do not stop/reverse pulmonary fibrosis [6]. Individual clinical trials with these approved treatments have not been powered to show mortality benefit, but analyses of pooled data from clinical trials and observational studies suggest improvement in life expectancy [6]. However, real-world data from heterogeneous IPF registries have shown that only 55–62% of patients diagnosed with IPF were receiving treatment with nintedanib or pirfenidone at enrolment [7]. In untreated patients, the median survival time after diagnosis is approximately 3–5 years [8–10]. Therefore, there remains a high unmet need for more efficacious and better-tolerated treatments in combination with standard of care or as a monotherapy for patients living with IPF.

Elevated levels of lysophosphatidic acid (LPA) and autotaxin have been observed in patients with IPF [11, 12]. LPA is a bioactive lipid involved in many physiological and pathological processes that activate LPA receptors, which have been implicated in the development of IPF [12–14]. LPA drives profibrotic and inflammatory processes by inducing cellular responses, including proliferation, migration, inflammation, and ultimately fibrosis [10, 12]. Studies have demonstrated LPA-induced cellular responses in fibroblasts that enhance the survival and activation of macrophages, which contribute to the fibrotic process [12, 15–17]. Fibroblast activation increases autotaxin secretion, an extracellular enzyme that catalyses the biosynthesis of LPA, creating a positive feedback loop that sustains and amplifies the fibrotic response [10, 15]. Therefore, LPA and autotaxin have been identified as therapeutic targets for the treatment of IPF.

Despite the failure of large phase III clinical trials with ziritaxestat and a phase II clinical trial with BBT-877 in patients with IPF, other compounds targeting the autotaxin–LPA pathway are currently being investigated in phase II and III clinical trials [18–24]. BI 1819479 is a very potent small molecule that inhibits the LPA pathway. Oral treatment with BI 1819479 was shown to have acceptable safety and tolerability in preclinical studies, and therefore advanced to four phase I studies with healthy volunteers [25–28]. Here, we describe the trial design of the phase II trial of BI 1819479 in patients with IPF.

## Materials and methods

### Trial design

This is a phase II (ClinicalTrials.gov Identifier: NCT06335303), randomised, double-blind, placebo-controlled, dose-finding trial evaluating the efficacy, safety and tolerability of three different oral doses of BI 1819479 in patients with IPF (figure 1). This multicentre trial will include approximately 300 enrolled patients across 28 countries (supplementary figure S1). Screening will be conducted to determine eligibility (visit 1). Patients will be randomised at the start of the study period (visit 2), which will allow for the collection of clinical and safety information and review of all inclusion and exclusion criteria. Trial participants will be randomised in a 2:1:1:1 ratio to one of four treatment groups: dose one of BI 1819479, dose two of BI 1819479, dose three of BI 1819479, or placebo, respectively. All trial participants will receive treatment and undergo assessments for a minimum of 24 weeks (visit 2 to visit 8). Following this period, patients will continue the same treatment and have assessments up to 52 weeks. Patients will be treated until either they complete 52 weeks of treatment or until 24 weeks after randomisation of the last patient (end-of-treatment visit within 2 weeks), whichever comes first. After their end-of-treatment visit, patients will receive a follow-up phone call after 4 weeks (±7 days) and have a follow-up (end-of-trial) visit after a minimum of 8 weeks (±3 days). Extending treatment beyond 24 weeks allows for the collection of more long-term efficacy data (more stable treatment estimate of the primary end-point) and long-term safety data without prolonging the trial.

**FIGURE 1 F1:**
[figure not shown]
Trial design. ^#^: Screening may be extended up to 6 weeks to account for possible missing eligibility results, administrative, or organisational reasons. ^¶^: Treatment remains the same during the whole treatment period; trial patients will end treatment at different time points, starting from week 24 up to week 52.

Randomisation will be stratified by background use of currently approved IPF treatments (with or without nintedanib/pirfenidone). The subgroup without background treatment will include patients not receiving nintedanib/pirfenidone in the 12 weeks prior to trial entry. Patients who are on a stable dose of nintedanib/pirfenidone for at least 12 weeks prior to trial entry and plan to remain on this treatment for the duration of the trial will constitute the subgroup with background IPF treatment. Randomisation will be monitored to achieve a distribution of patients of at least 20% without background treatment with nintedanib/pirfenidone and approximately 80% with background nintedanib/pirfenidone.

Subgroup analyses will include sex, age and the background treatment at baseline. In addition, the subgroup of patients receiving background treatment will be further partitioned into patients receiving each specific treatment (*i.e.* nintedanib/pirfenidone).

A summary of the trial design is provided as an infographic in supplement S1.

### Discontinuation of treatment

Patients may discontinue trial treatment temporarily or permanently. Those who permanently discontinue will perform an end-of-treatment visit at the time of discontinuation, followed by a safety follow-up phone call 4 weeks (±7 days) later and an end-of-trial visit at minimum 8 weeks (±3 days) after the last dose. Temporary interruption of BI 1819479 is permitted for specific cases (*e.g.* surgery, adverse events or other diseases), use of restricted concomitant medications or hepatic injury. Resumption of treatment is permitted if medically justified. Additional information is provided in supplement S2.

### Patient population

All inclusion and exclusion criteria are reported in table 1. Patients aged ≥40 years will be eligible for the trial if they have an IPF diagnosis based on ATS/ERS/JRS/ALAT 2022 guidelines, as confirmed by the investigator by chest high-resolution computed tomography (HRCT) scan with usual interstitial pneumonia (UIP) or probable UIP pattern within a clinical context consistent with a diagnosis of IPF [4]. Before randomisation, all HRCT scans will be sent for central review. Patients are also required to have forced vital capacity (FVC) ≥45% of predicted normal at screening and diffusing capacity of the lungs for carbon monoxide (*D*_L__CO_) corrected for haemoglobin ≥25% of predicted normal at screening. Patients with and without background treatment (nintedanib/pirfenidone) will be included. Patients who are on a stable background treatment with nintedanib/pirfenidone at the time of screening and randomisation are planned to continue this background treatment during the trial. Trial patients not receiving approved background treatment for IPF at enrolment and randomisation will be allowed to initiate an approved treatment in case of IPF progression and/or exacerbation (by investigator judgement) after the first 12 weeks of treatment.

**TABLE 1 TB1:** Inclusion and exclusion criteria

Inclusion criteria
Patients ≥40 years old at the time of signed informed consent. Signed and dated written informed consent in accordance with ICH GCP and local legislation prior to admission to the trial. Diagnosis of IPF: o based on the 2022 ATS/ERS/JRS/ALAT Guideline as confirmed by the investigator based on chest HRCT scan taken within 12 months of screening and, if available, surgical lung biopsy or transbronchial lung cryobiopsy, o and “UIP” or “Probable UIP” HRCT pattern consistent with the clinical diagnosis of IPF, as confirmed by central review prior to randomisation. ▪ Patients with “Indeterminate for UIP” HRCT findings are eligible if a clinical diagnosis of IPF can be confirmed locally based on (historical) surgical lung biopsy or transbronchial lung cryobiopsy demonstrating a “UIP” or “Probable UIP” histopathology pattern. ▪ Trial patients with HRCT findings suggestive of an “alternative diagnosis” are eligible if a clinical diagnosis of IPF can be confirmed locally based on (historical) surgical lung biopsy or cryobiopsy demonstrating a “UIP” histopathology pattern. Patients may be either: o on stable therapy^#^ with nintedanib or pirfenidone for at least 12 weeks prior to screening and planning to stay on this background treatment after randomisation. Combination of nintedanib plus pirfenidone is not allowed; o not on treatment with nintedanib or pirfenidone for at least 12 weeks prior to screening period (*e.g.* either AF-treatment naive or previously discontinued) and not planning to start or re-start background AF treatment. FVC≥45% of predicted normal at screening. *D*_L__CO_≥25% of predicted normal corrected for haemoglobin at screening. Women of childbearing potential (WOCBP)^¶^ must use highly effective methods of birth control with low user dependency and additional barrier contraception for male partners (use of condom) until end of follow-up period. The WOCBP must conduct regular pregnancy testing (at least monthly) and the trial medication must be discontinued in case of pregnancy. Male trial patients with WOCBP partners must use contraception (condom) to avoid exposure *via* seminal fluid. Female partners of male trial patients must use highly effective methods of contraception during treatment until end of follow-up period.

Exclusion criteria
Acute exacerbation of IPF within at least 12 weeks prior to screening and/or during the screening period (investigator-determined). Treated with immunosuppressive medications (other than oral corticosteroids) or prednisone >15 mg·day^−1^ or equivalent for respiratory or pulmonary reasons. Patients who must or wish to continue the intake of restricted medications (table 2) or any drug considered likely to interfere with the safe conduct of the trial. The patient is currently enrolled in another investigational device or drug trial, or their screening occurs less than 30 days or five half-lives (whichever is longer) after completing a previous investigational device or drug trial or receiving other investigational treatments. Patients with a significant disease or condition other than the IPF under trial, which, in the opinion of the investigator, may put the patient at risk because of participation, interfere with trial procedures or cause concern regarding the patient's ability to participate in the trial or any medical condition that could lead to a life expectancy <12 months. Relevant airways obstruction (pre-bronchodilator FEV_1_/FVC <0.7) at screening. In the opinion of the investigator, other clinically significant pulmonary abnormalities. Lower respiratory tract infection requiring treatment within 4 weeks prior to screening. Any documented active or suspected malignancy or history of malignancy within 5 years prior to screening, except appropriately treated basal cell carcinoma or squamous cell carcinoma of the skin, or *in situ* carcinoma of uterine cervix. Major surgery (major according to the investigator's assessment) performed within 3 months prior to screening or planned during the course of the trial. Being on a lung transplant list is allowed. Patients not expected to comply with the protocol requirements or not expected to complete the trial as scheduled (*e.g.* chronic alcohol or drug abuse or any other condition that, in the investigator's opinion, makes the patient an unreliable trial patient). Previous randomisation in this trial; re-screening is allowed. Hypersensitivity to the drug or its excipients. Women who are pregnant, breastfeeding, or plan to become pregnant while in the trial. Any vulnerable person (defined as: pregnant or breastfeeding women; persons deprived of their liberty; minors; persons who may have insufficient power, intelligence, education, resources, strength, or other needed attributes to protect their own interests; or unable to explicitly give consent), as per local regulation. Other clinically significant concomitant disease state (*e.g.* renal failure, hepatic dysfunction or cardiovascular disease) in the opinion of the investigator. Any condition not covered by any of the other exclusion criteria which, in the investigator's opinion, might jeopardise the patient's safety or compliance with the protocol. History of stem cell therapy for the treatment of pulmonary fibrosis.

AF: antifibrotic; ALAT: Latin American Thoracic Association; ATS: American Thoracic Society; *D*L_CO_: diffusing capacity of the lungs for carbon monoxide; ERS: European Respiratory Society; FEV_1_: forced expiratory volume in 1 s; FVC: forced vital capacity; GCP: Good Clinical Practice; HRCT: high-resolution computed tomography; ICH: International Council for Harmonisation of Technical Requirements for Pharmaceuticals for Human Use; IPF: idiopathic pulmonary fibrosis; JRS: Japanese Respiratory Society; UIP: usual interstitial pneumonia; WOCBP: women of childbearing potential. ^#^: Stable therapy is defined as the individually and generally tolerated regimen of either nintedanib or pirfenidone (no dose changes) for at least 12 weeks prior to screening. ^¶^: WOCBP (*i.e.* fertile, following menarche and until becoming postmenopausal, unless permanently sterile). Permanent sterilisation methods include hysterectomy, bilateral salpingectomy and bilateral oophorectomy. Tubal ligation is not considered as a method of permanent sterilisation. A postmenopausal state is defined as no menses for 12 months without an alternative medical cause.

Patients with relevant airway obstruction (pre-bronchodilator forced expiratory volume in 1 s/FVC<0.7) at screening, acute exacerbation of IPF within 12 weeks prior to screening and/or during the screening period (investigator-determined), being treated with immunosuppressive medications (other than oral corticosteroids) or prednisone >15 mg·day^−1^ or equivalent for respiratory or pulmonary reasons, or having a lower respiratory tract infection requiring treatment within 4 weeks prior to screening will be excluded from the trial. Patients taking a concomitant medication listed in table 2 will not be eligible for the trial. A historical chest HRCT scan will be used to determine eligibility (confirmed locally), as long as it is performed within 12 months prior to screening. If the historical scan is unavailable, or the available scan does not meet the required image acquisition specification, the HRCT scan may be performed during screening, provided all other eligibility criteria are fulfilled. If previously obtained, surgical lung biopsy or transbronchial lung cryobiopsy may be used to locally confirm IPF diagnosis.

**TABLE 2 TB2:** Concomitant medication restrictions

Medication	Prior to trial^#^	Screening period	Treatment period	Follow-up period
Strong inhibitors and inducers of CYP3A4	Permitted^¶^	Permitted^¶^	Not permitted	Not permitted
Strong inhibitors of UGTIA4	Permitted^¶^	Permitted^¶^	Not permitted	Not permitted
p-gp inhibitors and inducers	Permitted^¶^	Permitted^¶^	Not permitted	Permitted
Stem cell therapy for the treatment of pulmonary fibrosis	Not permitted	Not permitted	Not permitted	Not permitted
Immunosuppressive medications used for respiratory or pulmonary reasons (other than oral steroids)	Permitted^+^	Not permitted	Not permitted	Permitted
Prednisone >15 mg·day^−1^ or equivalent used for respiratory or pulmonary reasons^§^	Permitted	Not permitted	Not permitted^f^	Permitted

IPF: idiopathic pulmonary fibrosis; p-gp: p-glycoprotein. ^#^: Duration of restriction before screening (see exclusion criteria). ^¶^: Strong CYP3A4, p-gp inhibitors and inducers, and UGT1A4 inhibitors should not be taken within five half-life times prior to randomisation. ^+^: Referring to historical episodes of intake, permitted unless the treatment is ongoing at time of screening. ^§^: Inhaled, intranasal, intra-articular and topical corticosteroids are allowed. ^f^: Prednisone >15 mg·day^−1^ or equivalent can be prescribed during the treatment period in case of (suspected) acute IPF exacerbation and other underlying conditions.

### End-points

The primary end-point is the annual rate of decline in FVC (mL·year^−1^) assessed over a treatment period up to a maximum of 52 weeks. The secondary end-point is the absolute change from baseline in FVC (mL) at week 24. Further end-points include time to clinically meaningful events (disease progression or initiation of background treatment), patient-reported outcomes, additional lung function end-points for FVC and *D*_L__CO_, exploratory HRCT assessment (absolute change from baseline in quantitative lung fibrosis and quantitative ILD scores at week 24), and pharmacokinetic and pharmacodynamic end-points. The detailed list of end-points is reported in table 3.

**TABLE 3 TB3:** End-points

**Primary end-point**	The annual rate of decline in FVC (mL·year^−1^) assessed over a treatment period up to a maximum of 52 weeks.
**Secondary end-point**	The absolute change from baseline in FVC (mL) at week 24.
**Further end-points**	**Clinical meaningful events** Time to the first occurrence of any of the components of the composite end-point: first acute IPF exacerbation, first hospitalisation for respiratory cause, or death (whichever occurs first) over the duration of the trial. Time to initiation of background therapy over the duration of the trial (in the group of trial patients without background treatment). **Patient-reported outcomes** Absolute change from baseline in L-PF symptoms dyspnoea, cough and fatigue domain scores, symptoms total and impact score at weeks 24 and 52. Absolute change from baseline in PGI-S of shortness of breath, cough and fatigue, overall symptoms, impact of symptoms on daily life and activities, and overall health status scale scores at weeks 24 and 52. PGI-C of shortness of breath, cough, fatigue, overall symptoms, impact of symptoms on daily life and activities, and overall health status assessment status at weeks 24 and 52. **Lung function** Time to absolute decline in FVC % predicted of >10% from baseline or death up to week 52. Time to a relative decline from baseline in FVC % predicted of >10% or death up to week 52. Time to absolute decline from baseline in FVC % predicted of >5% or death up to week 52. Time to a relative decline from baseline in FVC % predicted of >5% or death up to week 52. Time to absolute decline in *D*_L__CO_ % predicted of >15% from baseline or death up to week 52. Absolute change from baseline in FVC % predicted at weeks 24 and 52. Absolute change from baseline in FVC (mL) at week 52. Absolute change from baseline in *D*_L__CO_ % predicted at weeks 24 and 52. **HRCT exploratory assessment^#^** Absolute change from baseline in QLF (%) at week 24. Absolute change from baseline in QLF (mL) at week 24. Absolute change from baseline in QILD (%) at week 24. Absolute change from baseline in QILD (mL) at week 24. **Pharmacokinetics** Descriptive statistics will be used to evaluate pre- and post-dose BI 1819479 concentrations. **Pharmacodynamics** LPA (18:2) concentration in plasma. Soluble protein biomarkers: MMP-7, KL-6, ICAM-1, CCL-18, SP-D, CA-125, CA19.9, CTGF, autotaxin. Neoepitope biomarkers: C3 M, C6 M, PRO-C3, PRO-C6.

CA-125: cancer antigen 125; CCL-18: chemokine (C-C motif) ligand 18; *D*_LCO_: diffusing capacity of the lungs for carbon monoxide; CTGF: connective tissue growth factor; FVC: forced vital capacity; HRCT: high-resolution computed tomography; ICAM-1: intercellular adhesion molecule 1; IPF: idiopathic pulmonary fibrosis; KL-6: Krebs von den Lungen 6; LPA: lysophosphatidic acid; L-PF: living with pulmonary fibrosis; MMP-7: matrix metalloproteinase 7; PGI-C: Patient's Global Impression of Change; PGI-S: Patient's Global Impression of Severity; PRO-C3: propeptide of type III collagen; PRO-C6: propeptide of type VI collagen; QILD: quantitative interstitial lung disease; QLF: quantitative lung fibrosis; SP-D: surfactant protein D. ^#^: Participation in the HRCT exploratory assessment is optional, at the discretion of the investigator and the trial patient and is not a prerequisite to participate in the trial.

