The secondary end-point is the assessment of change in FVC between treatment groups at week 24 using a restricted maximum likelihood (REML)-based mixed model for repeated measures (MMRM). All further end-points will be considered exploratory in nature. Continuous end-points will be analysed descriptively as well as using a REML-based repeated measures approach. Time-to-event outcomes will be analysed using Cox proportional hazards models with Kaplan–Meier plots. Plasma concentrations and exploratory biomarkers of BI 1819479 will be analysed descriptively. Missing data will not be imputed in the primary end-point analysis, except for death, for which a poor outcome will be assigned. Additional details on statistical methods are available in the supplementary material.

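### Time to initiation of background therapy is the only one of seven time-to-event end-points that does not count death, so a Kaplan–Meier plot of it would overstate the proportion starting treatment

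*Protocol article*

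**What the plan says.** Table 3 of the protocol article, under Further end-points, contains seven time-to-event end-points. Six count death:

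- the clinical composite, "first acute IPF exacerbation, first hospitalisation for respiratory cause, or death (whichever occurs first) over the duration of the trial"
- four end-points on a fall in FVC % predicted, with thresholds of 10% and 5%, each in an absolute and a relative form; one of them reads "Time to absolute decline in FVC % predicted of >10% from baseline or death up to week 52", and the other three likewise count death
- the corresponding end-point for an absolute fall of more than 15% in DLCO % predicted, which also counts death

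The seventh does not: "Time to initiation of background therapy over the duration of the trial (in the group of trial patients without background treatment".

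Statistical methods gives one analysis for all seven: "Time-to-event outcomes will be analysed using Cox proportional hazards models with Kaplan–Meier plots". It names no competing-risk method and states no censoring rule, calls all further end-points exploratory, and refers to supplementary material for detail. That supplement is not available here.

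Patient population sets out when an untreated patient may start an antifibrotic. Such patients "will be allowed to initiate an approved treatment in case of IPF progression and/or exacerbation (by investigator judgement) after the first 12 weeks of treatment".

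**The concern.** Death is a competing event for starting a treatment: once it occurs, initiation is impossible. A Kaplan–Meier curve that censors the dead treats them as if they could still start later. Its complement then estimates initiation in a hypothetical population without deaths, not the proportion of randomised patients who start.

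Two features of the plan make this relevant. Initiation is tied to progression or exacerbation, in a disease whose course the Background describes as ending in death, so the two events are plausibly related. And in the first 12 weeks a patient can die but may not yet initiate, so some patients leave the risk set before the event is even permitted.

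What is at stake is interpretation. The end-point stands under the heading of clinically meaningful events, where fewer initiations on active drug invite the reading that patients did better. An arm can have fewer initiations partly because more of its patients died.

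**Working it through.** **Count.** Seven time-to-event end-points in Table 3: six with death, one without.

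**Size of the group.** About 300 patients (Trial design), with at least 20% without background treatment (text below Figure 1) or 33% under the other planning scenario (Sample size determination, 100% − 67%). 300 × 0.20 = 60 and 300 × 0.33 = 99. With 2:1:1:1 allocation, 60 splits into one arm of 24 and three of 12; 99 splits into one of about 40 and three of about 20.

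**Kaplan–Meier against actual incidence.** The plan gives no initiation or death rate for this group, so both are assumed. Let l be the initiation hazard, acting only after week 12, and m the death hazard from randomisation, both constant and per year. At week 52:

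- 1 − KM with deaths censored = 1 − exp(−l × 40/52)
- actual cumulative incidence = exp(−m × 12/52) × l/(l + m) × [1 − exp(−(l + m) × 40/52)]

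For l = 0.6 and m = 0.1:

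- 1 − KM = 1 − exp(−0.4615) = 1 − 0.6303 = 37.0%
- incidence = 0.9772 × 0.8571 × (1 − 0.5836) = 34.9%
- excess = 2.1 points

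| l | m | 1 − KM | incidence | excess (points) |
|---|---|---|---|---|
| 0.3 | 0.05 | 20.6% | 20.0% | 0.6 |
| 0.3 | 0.2 | 20.6% | 18.3% | 2.3 |
| 0.6 | 0.1 | 37.0% | 34.9% | 2.1 |
| 1.0 | 0.05 | 53.7% | 52.2% | 1.5 |
| 1.0 | 0.2 | 53.7% | 48.0% | 5.7 |

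At week 24 (12/52 in place of 40/52 in both formulas) the same grid gives 0.1 to 1.4 points.

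**Using the one survival figure in the article.** The Background gives a median survival of about 3–5 years after diagnosis in untreated patients, so m = ln 2/3 = 0.231 or ln 2/5 = 0.139. If 1 − KM at week 52 is 20%, actual incidence is 17.4% (3 years) or 18.4% (5 years); if it is 40%, incidence is 35.0% or 36.9%. A selected trial population probably has lower mortality. With an assumed 10-year median, the figures are 19.2% and 38.4%.

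**Linked risks.** The formulas above treat the two hazards as unrelated. In a simulation with 5-year median survival and a gamma frailty shared by both events, 1 − KM was 17.1% against an actual 15.8% (frailty variance 1), and 15.1% against 14.1% (variance 2). The overstatement does not depend on independence.

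**Why the hazard ratio alone does not show benefit.** Take 20% initiation and 3-year median survival on placebo. The cumulative hazards to week 52 are −ln 0.8 = 0.223 for initiation and 0.231 for death. Suppose that active drug has an initiation hazard ratio of 0.6 and a death hazard ratio of 1.5. The cause-specific hazard ratio for initiation is 0.60. The cumulative hazard ratio for initiation or death is (0.6 × 0.223 + 1.5 × 0.231)/(0.223 + 0.231) = 0.480/0.454 ≈ 1.06. The first figure is correct as a cause-specific quantity but would mislead if read as overall benefit.

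**The case against.** **No censoring rule is stated.** This is true. A reader might infer that the plan explicitly censors deaths. It does not say so, and the supplement or analysis plan may deal with it. But the article does fix both the definition without death and the Kaplan–Meier and Cox methods, and with that pairing censoring is what follows unless another rule is added.

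**The Cox comparison is not wrong.** This stands. With deaths censored, the model estimates a valid cause-specific hazard ratio for initiation. The problem is confined to reading the curve as a probability and to reading fewer initiations as benefit.

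**The link between dying and initiating is assumed.** A reader might infer that the patients removed are those killed by the same process that triggers initiation. The article gives no causes of death, and deaths from any cause compete. The overstatement needs no such link.

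**Deaths are visible elsewhere.** The clinical composite covers the same period and the lung-function end-points also count death. This helps, but they mix death with other events and, as listed, are not confined to the untreated group.

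**Leaving death out is legitimate.** This also stands. The end-point measures use of a treatment, a different question from the other six. Adding death would change it: at 20% initiation, the 52-week composite would be 30.4% (5-year median survival) or 36.5% (3-year), so deaths would supply much of it.

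**The bias is small beside the noise.** With 12 patients at 37%, the standard error is √(0.37 × 0.63/12) ≈ 14 points, far above the 2.1-point excess. This supports a low rating; it is no reason to plot the wrong quantity.

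**Conclusion.** The point holds as a minor one. One of seven time-to-event end-points does not count death, and the stated method includes nothing for competing events. Used as written, the Kaplan–Meier complement would overstate the week-52 proportion starting an antifibrotic by about 0.6 to 5.7 percentage points. That range rests on assumed constant hazards, no initiation before week 12 and censoring of deaths; its top needs the highest value of both hazards.

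A reader might go further and conclude that a single death could reverse the comparison between arms. One death is 1/12, about 8%, of the smallest arm (about 5% of an arm of 20), but no reversal of the planned Cox comparison has been shown. The example with a ratio of 1.06 concerns a different end-point under chosen hazard ratios.

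Nothing decisive rests on this end-point. It is exploratory, concerns about 60–99 patients, and proof of concept depends on FVC slope, where death is assigned a poor outcome.

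**What to change.** Keep the end-point definition. For this end-point only:

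1. Replace the Kaplan–Meier plot with an Aalen–Johansen cumulative incidence curve by arm, with death as a competing event.
2. Label the Cox result as a cause-specific hazard ratio.
3. Show the number of deaths by arm in the untreated group beside it.
4. If wanted, add time to initiation or death as a sensitivity analysis, not as the definition.

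The cost is a line or two in the analysis plan. Dates of initiation are needed for the end-point anyway and deaths for the other six, so no new data are required, and sample size and the primary analysis are untouched. If the supplement or analysis plan already says this, a cross-reference is enough.
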